## **5. DISEASE DESCRIPTION**

### **Experimental design 1**

Patients with a clinically definite diagnosis of FMD based on Gupta and Lang diagnostic criteria (1) and 150 matched HC consecutively recruited by Unit 1 (75 patients and 75 HC) and Unit 2 (75 patients and 75 HC) (WP1).

### **Experimental design 2**

Patients with "organic" motor disorders (50 patients with weakness due to peripheral neuromuscular disorders; 50 with ET according to the 2018 consensus criteria (2); 50 with idiopathic adult-onset dystonia) recruited by Unit 1 (75 patients) and 2 (75 patients) (WP4)

### Experimental design 3

Patients with a clinically definite diagnosis of FMD based on Gupta and Lang diagnostic criteria (1).

## 6. METHODS AND INTERVENTIONS

### Experimental design 1

Subjects will be assessed at each center by a neurologist specialized in movement disorders. At the enrollment, demographic and clinical data will be collected for each patient according to the Italian Registry of Functional Motor Disorders (IRFMD) (7). Clinical motor outcomes will be measured with the objective-rated Simplified Functional Movement Disorders Rating Scale (SFMDRS) (8); fatigue, pain, anxiety, depression, alexithymia, and Quality of Life (QoL) will be assessed through the Multidimensional Fatigue Inventory Scale (MFI-20), Beck Anxiety Inventory (BAI), Beck Depression Inventory (BDI II), and 12-item Short-Form Health Survey (SF-12) (8). FMD and HC will undergo 3T MRI brain scans (Radiologia BR, AOUI Verona). With up-to-date tools, cortical thickness metrics, GM volumes, and resting-state functional connectivity of sensorimotor and non-motor brain regions will be analyzed (9-12). Assessments will be carried out on three days (the first day clinical assessment; the second day the neurophysiological assessments (Neurologia A, AOUI Verona); the third day the Imaging assessment. MRI brain scan will be performed at the Policlinico GB Rossi.

We will develop behavioral, neurophysiological, and MRI biomarkers for each patient and HC in the motor, exteroceptive, interoceptive and cerebral domains (see methods and interventions). Unit 1 and 2 will perform the same behavioral, neurophysiological, and MRI tests on FMD and HC. 3T MRI data will be processed by Unit 3 to estimate brain structural and functional MRI features of sensorimotor and non-motor networks (WP2). The diagnostic biomarker algorithm through XAI methods will be developed by Unit 2 (WP3). XAI methods will be developed to identify and characterize numerical biomarkers and understand the “why” and the “how” of the machine learning outcomes. XAI is the new frontier of Artificial Intelligence (AI) in that it provides a mean of interpreting the behavior of complex algorithms, enabling their exploitability in the biomedical field. Deep learning will be used, and visualization and interpretability methods will be exploited to develop a biomarker-based diagnostic algorithm. eXplainable AI (XAI) analysis. Details are reported in the Statistical Analysis section.

The implementation of machine learning algorithms will be done using the KNIME analytics platform (v. 4.2.1), widely used in biomedical studies. **The software is for research purposes only and not for diagnostic purposes. Data analysis will be anonymized for privacy protection, removing personally identifiable information from data sets (i.e., patients' number will be changed into a range of values with logical boundaries).** In this study, binary supervised classification will be applied with learning derived from decision tree-based (tree-based) and instance-based (instance-based) algorithms. Machine learning input features will include clinical and neurophysiological variables and data extracted from neuroradiological imaging. Feature importance will also be calculated using the Random Forest algorithm to identify the most relevant input features for classification.

### Experimental design 2

The same diagnostic biomarker algorithm identified in experiment 1 will be tested in patients with organic motor disorders (WP4) to identify disease-specific hallmarks of FMD. Structural and functional MRI data will be processed by Unit 3. The diagnostic biomarker algorithm through XAI methods will be tested by Unit 2.

### Experimental design 3

A physician expert in movement disorders will assess patients at each time point through validated clinical scales to assess motor and non-motor symptoms, depression, anxiety, alexithymia, and QoL as reported in the Methodologies section. A task-based fMRI paradigm to evaluate functional brain reorganization of sensorimotor and non-motor networks induced by rehabilitation and correlations with clinical improvement will be

implemented and performed before rehabilitation (T0) and at 3-month follow-up (T1) (5,6). fMRI data will be analyzed by Unit 3. The diagnostic biomarker algorithm through XAI methods will be tested by Unit 2 before and after rehabilitation.

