### **4. SUBJECTS**

#### **Experimental design 1.**

150 patients with a clinically definite diagnosis of FMD based on Gupta and Lang diagnostic criteria (1) and 150 matched HC consecutively recruited by Unit 1 (75 patients and 75 HC) and Unit 2 (75 patients and 75 HC) (WP1).

Inclusion criteria for patients will be age higher or equal to 18 years and a clinically definite diagnosis of FMD (1). Exclusion criteria for patients will be Mini-Mental State Examination score lower or equal to 24; physical impairment precluding signing the informed consent for participation; certified neurological and/or psychiatric comorbidities (i.e., neuropathy, seizures, major depression); contraindications for 3T MRI.

Inclusion criteria for HC will be age higher or equal to 18 years; Exclusion criteria for HC will be Mini-Mental State Examination score lower or equal to 24; physical impairment precluding signing the informed consent for participation; certified neurological and/or psychiatric comorbidities (i.e., neuropathy, seizures, major depression); contraindications for 3T MRI.

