### **Experimental design 2.**

150 additional patients with "organic" motor disorders (50 patients with weakness due to peripheral neuromuscular disorders; 50 with ET according to the 2018 consensus criteria (2); 50 with idiopathic adult-onset dystonia) recruited by Unit 1 (75 patients) and 2 (75 patients) (WP4). ET patients will undergo a neurological assessment by a movement disorder specialist. Patients with idiopathic adult-onset cervical or limb dystonia, either focal or as part of a segmental/multifocal dystonia, will be diagnosed according to published criteria (3). Patients with muscle diseases including idiopathic inflammatory myopathies, sporadic inclusion body myositis and limb-girdle muscular dystrophies will be evaluated according to published criteria (4).

We will assess the same biomarkers identified in the diagnostic biomarker algorithm (experiment 1) in 150 patients with organic motor disorders recruited from Unit 1 and Unit 2 (2-4).

Additional exclusion criteria will be score >2 on the Tremor Research Group Essential Tremor Rating Assessment Scale; rest tremor and other neurological signs; current or past exposure to tremorigenic drugs. Demographic and clinical findings will be collected. Tremors and dystonia severity will be rated using the Fahn-Tolosa-Marin TRS and the Burke-Fahn-Marsden scale. Anxiety, depression, alexithymia, and QoL will be evaluated through the BAI, BDI II, and SF-12.

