## 11. SAMPLE SIZE CALCULATION

Sample size calculations are based on the simulations performed by Guo et al. 2010 (26). We will use Random Forests (RF) owing to their non-parametric nature that contributes to robust performance under settings of varying class conditional biomarkers distributions. Assuming a skewed distribution of the dataset and up to 100 neurophysiological and imaging features to include in the statistical analysis,  $k=1\%$  (where  $k$  is the percentage of biomarkers among  $n$  features measured per subject) and effect size for each biomarker  $< 0.3$ , we need a sample size of 150 subjects (75 patients with FMD and 75 HC, among all Units) using RF that ensures a statistical power  $>90\%$ , with a 4-fold cross-validation process. **To address concerns regarding the**

validity of cross-validation-based estimates in relatively small samples, we will pursue an additional external validation based on an independent test set of 150 subjects (75 patients with FMDs and 75 HC, among all Units). Finally, the diagnostic biomarker algorithm (experiment 1) will be tested against a population of patients of 150 patients with "organic" motor disorders of similar sample size (50 with weakness due to muscle diseases, 50 with ET, and 50 with dystonia, among all Units). Based on our previous study, for the rehabilitative study Unit 1 will enroll 34 patients, assuming  $\alpha = 0.05$ , power 90%, and T0-T1 rehabilitation effect size of 0.605 (mean difference 5.52; Standard deviation 9.11) on the primary outcome (SFMDRS) and a drop-out rate of 10%(8).

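### The classifier's feature set is contradictory, and the version that admits clinical variables does not exclude a scale that rates the diagnosis being predicted

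*Protocol*

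**What the plan says.** The protocol describes the inputs of the diagnostic algorithm in two ways.

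**Clinical inputs admitted.**
- Section 6, machine-learning paragraph: "Machine learning input features will include clinical and neurophysiological variables and data extracted from neuroradiological imaging".
- Section 3, the hypothesis after specific aim 3: the composite panel is clinical as well as neurophysiological and neuroimaging.
- Section 4, Experimental design 3: the T0 and T1 assessments repeat the clinical scales and biomarkers of the algorithm, wording that can be read as placing scales inside it.

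**Clinical inputs not mentioned.**
- Section 3, specific aim 1: the algorithm models behavioural, neurophysiological and MRI biomarkers.
- Section 6, biomarker lists for the motor, exteroceptive, interoceptive and cerebral domains: no rating scale appears.
- Section 11: the sample size assumes "up to 100 neurophysiological and imaging features to include in the statistical analysis".

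The case label is clinical: "Inclusion criteria for patients will be age higher or equal to 18 years and a clinically definite diagnosis of FMD (1"). The clinical measures named for experiment 1 are SFMDRS ("Clinical motor outcomes will be measured with the objective-rated Simplified Functional Movement Disorders Rating Scale (SFMDRS) (8")), the "Multidimensional Fatigue Inventory Scale (MFI-20), Beck Anxiety Inventory (BAI), Beck Depression Inventory (BDI II), and 12-item Short-Form Health Survey (SF-12) (8"), and registry data: "demographic and clinical data will be collected for each patient according to the Italian Registry of Functional Motor Disorders (IRFMD) (7").

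For the organic cohort, Section 4 (Experimental design 2) names these scales: "Tremors and dystonia severity will be rated using the Fahn-Tolosa-Marin TRS and the Burke-Fahn-Marsden scale", and "Anxiety, depression, alexithymia, and QoL will be evaluated through the BAI, BDI II, and SF-12".

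**The concern.** A diagnostic model should not take as input a variable that forms part of the reference standard or grades the condition that the standard establishes. FMD status is assigned by clinical examination. By its name and its use here, SFMDRS rates the severity of functional movement disorder, and registry items describing the functional signs are of the same kind. If such variables enter, the model partly predicts the diagnosis from itself.

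Three things are at stake.

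- **Aim 1.** Accuracy against healthy controls would be inflated. Random Forest importance, the stated tool for finding the most relevant features, would favour the scale over the neurophysiological and MRI measures that the project sets out to test.
- **Aim 2.** Specificity against organic disease is to be tested with the same algorithm. If that algorithm retains a scale that is not scheduled in organic patients, an input is missing.
- **Aim 3.** SFMDRS is the primary outcome of the rehabilitation sub-study (Section 11). Correlating change in an algorithm that contains SFMDRS with change in motor symptoms would partly correlate the scale with itself.

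**Working it through.** **The plan's own figure.** The training sample of 150 (75 FMD, 75 controls) with power above 90% comes from a cited simulation study whose settings are not in the protocol. No closed formula reproduces it, and this point does not depend on it. What matters is that the sizing text names neurophysiological and imaging features only. With up to 100 features and k = 1%, it expects 0.01 × 100 = 1 informative feature, with an effect size below 0.3.

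**Step 1: a single biomarker at the plan's ceiling.** Take 0.3 as a standardised mean difference d between two normal distributions. The protocol does not say that it is one.
- AUC = Φ(d/√2) = Φ(0.3/1.414) = Φ(0.212) = 0.584
- Best accuracy at 1:1 = Φ(d/2) = Φ(0.15) = 0.56

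**Step 2: a severity scale specific to the disorder.** Assume that the score is 0 in all controls and above 0 in a share s of FMD patients. The protocol gives no such share, so a range is shown.
- AUC = s + (1 − s)/2
- Accuracy of the rule that any score above 0 means FMD, at 1:1 = (1 + s)/2, which is the same number

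| s | AUC and accuracy |
|---|---|
| 0.80 | 0.80 + 0.10 = 0.90 |
| 0.90 | 0.90 + 0.05 = 0.95 |
| 0.95 | 0.95 + 0.025 = 0.975 |
| 1.00 | 1.00 |

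In the training set, s = 0.80 means 60 of 75 patients and 75 of 75 controls classified correctly: 135/150 = 0.90 from one variable, whatever the biomarkers contribute.

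**Step 3: would the independent test set reveal it?** No. Sections 11 and 12 describe a further 75 FMD patients and 75 controls, defined in the same way. A variable that grades the diagnosis separates those groups as well as it separates the training groups.

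**Step 4: scales by cohort, as listed.**

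| Scale | Experiment 1 | Organic cohort |
|---|---|---|
| SFMDRS | listed | not listed |
| MFI-20 | listed | not listed |
| BAI | listed | listed |
| BDI-II | listed | listed |
| SF-12 | listed | listed |

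Two of the five scales named for experiment 1 are not named for organic patients. The registry sentence in Section 6 also ties clinical data to patients, so it is not explicit that controls are scored. If they were not, a missing score would itself give away the label. That is a possibility, not something the protocol states.

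**The case against.** The strongest reply is that Section 6 says only that clinical variables enter and names no scale. The protocol's usual triple is behavioural, neurophysiological and MRI. The Section 6 sentence mentions no behavioural features, although gait, sensory attenuation and the heartbeat task are core measures, so *clinical* may simply stand for *behavioural*. Elsewhere scales are kept apart from biomarkers: specific aim 3 correlates the two, and Section 12 plans association studies with clinically relevant parameters. The sentence in Experimental design 3 can be read either way, and an item-level feature list could properly be left to an analysis plan.

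This stands in part. A reader might infer that the protocol definitely feeds SFMDRS and MFI-20 into the model; the text does not say so. But the protocol itself states two different feature sets, which goes beyond a missing detail, and the wording of Sections 3, 4 and 6 makes the inclusion of scales a fair reading that nothing rules out.

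A reader might also infer that aim 2 cannot run the same model. That goes too far. Experimental design 2 commits to assessing in organic patients the biomarkers that the algorithm identifies and to collecting clinical findings. Section 10 places those assessments in months 13–22, after model building in months 10–12, so a retained scale could still be added.

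Third, circularity does not extend to every scale. MFI-20, BAI, BDI-II and SF-12 are not described as diagnostic criteria. Their risk is that they separate ill from healthy people non-specifically, which aim 2 is designed to examine.

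Finally, feature importance and the explainability analyses would make a dominant scale visible. They would not remove the bias.

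**Conclusion.** The concern holds as a contradiction with a conditional consequence. The feature set must be reconciled, because one of the two descriptions allows variables that rate the diagnosis into a model trained to predict that diagnosis. If SFMDRS enters and behaves as assumed (0 in controls, above 0 in 80–100% of patients), it alone gives an AUC of 0.90–1.00, against about 0.58 for one biomarker at 0.3, and would dominate feature importance in both the training and the validation data. The range rests on the assumed score distribution, and the 0.58 rests on reading 0.3 as a standardised mean difference.

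For aim 2 the supported statement is narrower: if the algorithm retains SFMDRS or MFI-20, the assessments listed for the organic cohort do not supply that input. The documents do not support saying that all reported accuracy would be circular, or that aim 2 is impossible.

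**What to change.** Before model building starts in month 10:

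- Reword the Section 6 sentence so that the primary diagnostic classifier uses only the behavioural-task, neurophysiological and MRI features listed under the four biomarker domains.
- State that any variable that defines or rates the diagnosis (SFMDRS, registry items describing the functional signs) is excluded from it.
- Use the clinical scales only in the association analyses already planned in Section 12, or in a separately reported clinical benchmark. Limit that benchmark to items collected identically in FMD patients, controls and organic patients. From the present lists these could be BAI, BDI-II and SF-12, once their collection in controls is made explicit.
- Align the hypothesis in Section 3 and the T0/T1 sentence in Experimental design 3 of Section 4. Name the behavioural-task features in Section 11 alongside the neurophysiological and imaging ones.

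The cost is a few sentences and a matching feature list. No new data are needed. The sample size does not change, because Section 11 already sizes without clinical scales, provided the full list stays within its limit of 100 features. Apparent accuracy against healthy controls will be lower, but it can then be attributed to the biomarkers.

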**Biomarker development in the motor domain:**

- Contingent Negative Variation (CNV, amplitude), a slow negative EEG wave representing motor preparation and anticipatory attention to a forthcoming imperative cue (13-14). It will be evaluated by electroencephalogram.
- Pre-pulse inhibition of the blink reflex (R2 response magnitude of the blink reflex), an EMG signal reflecting sensorimotor gating at the subcortical level and an early automatic process (15). It will be evaluated by EMG.
- Single and dual-task posture and gait parameters using stabilometric and gait analyses (16). They will be assessed by spatio-temporal gait analysis and stabilometric assessment.

**Biomarker development in the exteroceptive domain:**

- Sensory attenuation (SA, ratio between the matched force and the target force), a proxy of sense of agency (17). It will be evaluated by using a custom-made force transducer which measures fingers' strength (Newton).
- Tonic vibration reflex (TVR, angles of the vibrated  $\bar{i}$  and the tracking arm) to assess proprioception (18-19). It will be evaluated by a physiotherapy vibrator [18].
- Somatosensory evoked potentials (SEP, amplitude) (20) reflecting the influence of high-level priors on the processing of bottom-up sensory data. It will be evaluated by EMG.
- Laser evoked potentials (LEP, N2/P2 amplitude), a non-invasive measure of the functional status of brain areas involved in nociceptive processing (14,21) assessed when attention is directed towards or away from the stimulated hand. It will be evaluated by EMG examination and YAP laser stimulator.

**Biomarker development in the interoceptive domain:**

Heartbeat Perception Task (HPT, objective/subjective Heart Rate HR, ratio) (22), a measure of processing of internal bodily signals by the CNS. Heart rate will be recorded with a Polar wrist-worn (model V800) wireless connected to the chest belt.

**Biomarker development in the cerebral domain:**

- Brain 3 Tesla MRI scans obtained from FMD, and HC will include T2-weighted FLAIR to exclude CNS lesions; 3D T1-weighted for morphometric analysis (cortical thickness and grey matter volumes); resting-state fMRI to assess functional connectivity of sensorimotor and non-motor networks (9-12).

**Rehabilitation protocol**

It is a validated 5-day rehabilitation protocol (2 h/day) within a multidisciplinary etiological framework followed by telemedicine program (8,23-25). The in-person 5-days rehabilitation program (2 h/day) will be aimed to re-establish normal movement patterns within a multidisciplinary etiological framework according to a validated rehabilitation protocol for FMD. Treatment will be tailored to the needs of each patient, following general treatment principles: education, exploration of how symptoms affect movement and posture; retraining movements using strategies based on redirection of attention; and development of a self-management plan. Details on the intervention have been described previously (8,23-25). On completion of the 5-days in-person rehabilitation program, the patients will undergo the telemedicine program during one out of the three weekly home-based sessions for 12 consecutive weeks (30 min/session, 1 session/week). It will consist of overground walking at different gait speed, walking backward and sideways, sit-to-stand activities, and squat exercises for lower limb weakness and gait and balance deficits. Bear weight on the hand and straddling a swiss ball will be used for upper limb weakness (31). During each session, the therapist had a video call with the patient via a smartphone or a computer connection according to the patient's availability and preference.

**7. END POINT**

- From experiments 1 and 2 we will determine which biomarkers are the hallmarks for FMD diagnosis identifying the key differences between FMD, HC, and organic movement disorders.
- From experiment 3, clinical and MRI biomarkers will be tested as predictive for rehabilitation outcomes by applying diagnostic biomarker algorithm before and after rehabilitation.
- We will provide specific and sensitive outcome measures and estimate sample sizes for future intervention trials FMD.

Flowchart.

| Activity                                                                                                                                   | Recruitment | Visit 1 | Rahab Intervention | Visit 2 |
|--------------------------------------------------------------------------------------------------------------------------------------------|-------------|---------|--------------------|---------|
|                                                                                                                                            |             | T0      |                    | T1      |
| Inclusion/exclusion criteria                                                                                                               | x           |         |                    |         |
| Consent for participation                                                                                                                  | x           |         |                    |         |
| Clinical and demographic information                                                                                                       | x           |         |                    |         |
| Collecting and developing behavioral, neurophysiological, and MRI biomarkers in Healthy controls and FMD patients*                         |             | X       |                    |         |
| Collecting and developing behavioral, neurophysiological, and MRI biomarkers in patients with organic motor disorders*                     |             | X       |                    |         |
| 5-day rehab protocol (2h/day) followed by 3-month telemedicine program (1 session/week; 12 weeks) °                             |             |         | X                  |         |
| Collecting and developing behavioral, neurophysiological, and MRI biomarkers in Healthy controls and FMD patients after rehab ° |             |         |                    | X       |
| Adverse events                                                                                                                             |             | X       | X                  | x       |
| Dropout rate                                                                                                                               |             | X       | X                  | X       |
| * Additional procedure                                                                                                                     |             |         |                    |         |

\* Additional procedures: University and research staff (research fellows) will carry out the assessment procedures

° in a sub-group of patients (n=34)

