#### **Specific aim 3**

To explore whether the validated biomarkers change after a multidisciplinary rehabilitation training and correlate them with changes in quality of life and motor and non-motor symptoms of FMD patients to determine their potential role in measuring treatment response and giving prognostic information.

We hypothesize that a composite panel of clinical, neurophysiological, and neuroimaging biomarkers covering motor, exteroceptive and interoceptive domains would be instructive in the diagnosis and prognosis of FMD from the earliest symptoms onset. It would allow the correct diagnosis of these patients early and delineate specific management pathways for future intervention trials with positive socio-economic impact.

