## 12. STATISTICAL ANALYSIS

eXplainable AI (XAI) analysis. First, ad-hoc models will be identified based on the available data, accounting for type (multi- modal), numerosity, completeness (missing data). Then, the models will be trained and validated following k-fold cross- validation and finally tested on a new (unseen) set of data to assess their generalization properties. Classical linear methods that are the most widespread in the clinical field will be used for benchmarking. Finally, we will apply XAI methods for assessing feature relevance, and consensus will be assessed under the assumption that this will provide information about the robustness of the outcomes (27-29). This will also be investigated through association studies with parameters holding clinical relevance.

Firstly, we will employ XAI analysis using the dataset from the first recruited 150 subjects (75 FMD and 75 HC). Secondly, external validation will be performed on an independent dataset of features collected on an additional sample of 150 subjects (75 FMD and 75 HC). Finally, the biomarkers identified in the diagnostic biomarker algorithm (experiment 1) will be tested against patients with organic neurological disorders recruited by Unit 1 and 2.

For the rehabilitation sub-study, descriptive statistics will include frequency tables for categorical variables and mean and standard deviation for continuous variables. The normality of data distribution will be checked with the Shapiro-Wilk test. Parametric (paired t-test) or non-parametric tests (Wilcoxon test) will be applied accordingly to compare the means for the two-time points (T0, T1). fMRI data will be analyzed using the SPM12 software. One-sample t tests will be used to evaluate significant mean brain activations during the task. Changes over time will be evaluated using a paired t test. All the longitudinal data deriving from the rehabilitation sub-study will be handled with a complex approach named Gaussian Process Panel Modeling (GPPM). GPPM provides great flexibility because of the large number of models it can represent. It allows classical statistical inference as well as machine learning inspired predictive modeling, with the advantage of obtaining person-specific predictions of treatment response (30).

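### The end point promises prediction of rehabilitation outcome, but every analysis stated for it measures change; no model relates T0 biomarkers to T1 outcome

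*Protocol*

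**What the plan says.** All references are to the protocol.

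- **Section 7, End point:** for experiment 3, "clinical and MRI biomarkers will be tested as predictive for rehabilitation outcomes by applying diagnostic biomarker algorithm before and after rehabilitation".
- **Section 3, Specific aim 3:** the purpose is "To explore whether the validated biomarkers change after a multidisciplinary rehabilitation training and correlate them with changes in quality of life" and in symptoms, and from this "to determine their potential role in measuring treatment response and giving prognostic information".
- **Section 2, Experimental design aim 3:** adds task-based fMRI at T0 and T1, and correlations of rehabilitation-induced brain reorganisation with clinical improvement.
- **Section 12, Statistical analysis:** after a Shapiro-Wilk check, "Parametric (paired t-test) or non-parametric tests (Wilcoxon test) will be applied accordingly to compare the means" at T0 and T1. Change in fMRI is also assessed by a paired t-test. Then: "All the longitudinal data deriving from the rehabilitation sub-study will be handled with a complex approach named Gaussian Process Panel Modeling (GPPM"), described as flexible and suited to predictive modelling, "with the advantage of obtaining person-specific predictions of treatment response (30").
- **Section 11, Sample size calculation:** 34 patients in one group, from alpha 0.05, 90% power, an "effect size of 0.605 (mean difference 5.52; Standard deviation 9.11) on the primary outcome (SFMDRS") and 10% drop-out.
- **Section 4, Experimental design 3:** the 34 are drawn at random from the 75 Unit 1 patients of experiment 1. The same scales and biomarkers are taken at T0 and T1.

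**The concern.** A predictor of rehabilitation outcome must be known before rehabilitation and then related to what happens later. A T0-T1 difference in the algorithm score is known only at T1, so it cannot forecast T1. If it moves together with the change in SFMDRS, that shows responsiveness, or a common cause of both changes, but not prognosis. A team following sections 7 and 12 as written could find that scores fall as patients improve and report the biomarkers as predictive without having tested this.

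Two related matters affect the same conclusion. Section 12 presents GPPM as giving predictions of response for each person, which two measurements in an uncontrolled group do not support without further assumptions. It also gives overlapping analyses of the T0-T1 SFMDRS data (paired t, Wilcoxon, GPPM) without saying which one decides.

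**Working it through.** **1. Stated analyses against the question.**

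| Stated analysis | Where | What it estimates | T0 biomarker to T1 outcome? |
|---|---|---|---|
| Algorithm applied before and after | 7 | Change in score | No |
| Biomarker change correlated with change in symptoms and quality of life | 3 | Association of two changes | No |
| fMRI reorganisation correlated with improvement | 2 | Association of two changes | No |
| Paired t or Wilcoxon; paired t for fMRI | 12 | Mean or typical change | No |
| GPPM | 12 | Not specified: no outcome, predictor or covariance form | Not stated |

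**2. The plan's own figure.** The effect size is 5.52/9.11 = 0.606, stated as 0.605. Assuming a two-sided test (sidedness is not stated):
- Normal approximation: n = ((1.960 + 1.282)/0.605)² = 28.7, so 29; 29/0.9 gives 33.
- Exact paired t: n = 31 with power 90.3%; 31/0.9 = 34.4, and 31 × 1.1 = 34.1.

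The stated 34 is therefore reproduced as a paired test of mean SFMDRS change. Expected completers are 34 × 0.9 = 30.6, about 31.

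**3. What 31 completers support for one biomarker.** With Fisher's z, the detectable correlation is r = tanh[(z for alpha + z for power)/√(n − 3)], two-sided 0.05:
- 80% power: tanh(2.802/√28) = 0.485
- 90% power: tanh(3.242/√28) = 0.546

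Adjusting for T0 SFMDRS replaces 28 by 27 and gives 0.492 and 0.554, so about 0.49 and 0.55 either way. Power at r = 0.3, 0.4 and 0.5 is 37%, 61% and 83%. The number of biomarkers to be tested is not stated. If it were 5, 10 or 20 with a Bonferroni correction, the 80% threshold would be about 0.57, 0.60 or 0.62.

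**4. GPPM with two occasions.** Section 12 refers to "compare the means for the two-time points (T0, T1"), so each person has two values per outcome. Write T0 = a + e₀ and T1 = a + b + e₁, where a is the person's level, b the person's own change and e the error, with equal error variance σ². Then:
- Var(T0) = Va + σ²
- Cov(T0, T1) = Va + Cab
- Var(T1) = Va + Vb + 2Cab + σ²

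These are three equations for four unknowns (Va, Vb, Cab, σ²). Counting the two means as well, there are 5 moments against 6 parameters.

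The variance of the observed change is Vb + 2σ². Taking 9.11 as the SD of the differences, as the paired calculation implies, this is 9.11² = 83.0. On its own that figure is compatible with no variation in individual response (Vb = 0, σ = 9.11/√2 = 6.44), with no error (Vb = 83.0), or with anything between. Without a control arm, an individual change also cannot be attributed to treatment.

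**5. Overlap with experiment 1.** Section 12 builds the algorithm on the first 75 FMD patients recruited and validates it on the next 75. If the sub-study draws evenly from both halves (an assumption), about 34 × 75/150 = 17 of its patients were used in training. Their scores would not be comparable with those of patients whom the model had never seen.

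**The case against.** The strongest reply is that the protocol contains all the data needed. Predicting a T1 outcome from a T0 biomarker requires only T0 and T1, both visits collect the same measures, GPPM is named with predictive modelling in mind, and the exact regression could sit in an SAP that is not shown. Aim 3 and the abstract are also worded as exploration. Much of this stands, and it limits the point. Four stronger readings may tempt a reader, and the documents do not support them.

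- **That two time points rule out prediction.** They do not; the remedy below uses only those two.
- **That GPPM cannot be fitted.** The protocol names no covariance form. A person effect plus noise has 2 parameters against 3 variance-covariance quantities and is identified, and a T0 predictor can enter the mean without a random slope. What fails is separating individual response from error without added constraints.
- **That the 90% power is misstated.** Section 11 claims it only for mean SFMDRS change.
- **That choosing the test by a normality check inflates type I error.** In simulations at n = 31 with skewed, zero-mean differences, the two-stage rule and Wilcoxon used alone agree: 16.4% against 16.5% for exponential differences, 11.0% against 10.9% for gamma with shape 2. The excess arises because Wilcoxon tests symmetry about zero, not the mean. When T0 and T1 scores are skewed but exchangeable, the two-stage error is about 5%. The protocol gives no distribution for the change, so no inflation can be charged to it.

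What the reply does not meet is that section 7 does name a method for testing prediction, and that method measures change. An SAP could add a model, but the protocol's wording would still be wrong.

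**Conclusion.** The point holds as a mismatch between claim and stated method. Section 7 says prediction will be tested, while the analyses in sections 2, 3, 7 and 12 give change or concurrent association, apart from an unspecified GPPM. The individual-prediction claim in section 12 is not supported by two uncontrolled measurements without constraints that the protocol does not state. The prognostic question can be answered with the planned data, but only weakly: about 31 completers detect a correlation of about 0.49 (80% power) or 0.55 (90%) for a single predictor. These figures assume a two-sided 0.05 test, 10% drop-out and no multiplicity. The case for naming one primary test rests on clarity and on agreement with the sample-size basis, not on any demonstrated error inflation. The change should be made, but the point does not affect the sizing of the mean-change comparison.

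**What to change.** 1. **Sections 7 and 12, prognostic analysis.** State it as T1 SFMDRS regressed on T0 SFMDRS plus one pre-specified T0 predictor. Report the partial association with a 95% CI and label it exploratory. The T0 algorithm score is a natural candidate, although it was trained to separate FMD from healthy controls and not to grade response. Compute it out of sample: from held-out folds for patients in the development set, and from the frozen model for the rest.
2. **Section 7, wording.** Describe the before-and-after application of the algorithm as a measure of change or responsiveness.
3. **Section 12, GPPM.** If it is used, keep it as secondary and state its form and constraints. Remove the claim of individual prediction of treatment response.
4. **Section 12, primary test.** Name the paired t-test of T0-T1 SFMDRS change. It matches the calculation in section 11 and the stated intention to compare means. Keep Wilcoxon as a sensitivity analysis.
5. **Section 11.** Add a sentence that 34 patients power the mean change only, with the detectable correlation of about 0.49.

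The cost is rewording of three sections, with no extra patients, visits or measurements. The individual-prediction claim is given up, and the prognostic result will be imprecise unless the association is strong.
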